### Study interventions

After completion of visit 1 (preliminary/baseline), and determination of patient’s eligibility to be enrolled in the study, participants will be randomized into one of the three arms of the study and be scheduled for the procedure visit. At this visit, the participants will either receive an intra-articular injection of WJ (treatment), HA (control), or saline (placebo control). Following the procedure, the participants will be periodically followed for 1 year. After the 3-month follow-up visit, patients injected with HA or saline will be offered the opportunity to cross over to the WJ group. If they decide to cross over, they will receive an injection of WJ and will follow the schedule of events for the WJ injection group beginning immediately after the injection follow-up visit.

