### Assessment points

Assessments for the study period will begin at visit 1 (preliminary/baseline). The patients will be assessed using the inclusion/exclusion criteria for eligibility in the study. The participants will then undergo a physical exam (PE) on the knee diagnosed with grade II/III OA, as well as a baseline plain radiograph for an up-to-date OA grade on the KL scale and a T2-weighted MRI to obtain a Magnetic Resonance Observation of Cartilage Repair Tissue (MOCART) score. The participants will also be required to complete baseline case report forms (CRFs) including the Numeric Pain Rating Scale (NPRS), Knee Injury and Osteoarthritis Outcome Score (KOOS), and patient satisfaction/survey, SF-36. Demographic information and medical history will also be collected. The participants will then be assessed for any adverse events at visit 2.2, immediately following their respective intra-articular injection, and at their procedure visit (visit 2.1) and be re-assessed for pain using the NPRS. Through visit 3 (24 h follow-up), visit 4 (48 h follow-up), and visit 5 (1 week follow-up), patients will be reassessed for pain using the NPRS. On visit 5 (1 week follow-up), visit 6 (6 weeks follow-up), and visit 7 (3 months follow-up), participants will undergo another PE as well as have their NPRS, KOOS, and 7-point Likert scale recorded. Plain radiographs will be taken on visits 6 and 7. At this point of the study, patients in the HA or saline arms will be offered the opportunity to cross over to the WJ arm and will follow the schedule of events beginning at visit 2.2. On visit 8 (6 months follow-up) and visit 9 (1 year follow-up), patients will undergo a PE as well as have their NPRS, KOOS, 7 point Likert scale, and SF-36 taken and recorded. In addition, plain radiographs will be taken again followed by an MRI on visit 9 for a MOCART score. All participants will have the opportunity to report any adverse events at each visit or at any time within the study.

The following are the primary endpoints:
To determine the safety of umbilical cord-derived Wharton’s jelly formulation (GeneXSTEM™)To assess the patient satisfaction

The following are the secondary endpoints:
To assess the change in patient-reported outcome measures, NPRS and KOOS, from baseline and between the groups at different time pointsTo assess the cartilage formation via MOCART at 1 year time point and compare it from baseline and between the groups

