On the other hand, despite the widespread use of HA, there is inconsistency in clinical studies pertaining to the effect of HA in knee OA. More randomized controlled trials with larger data set are required to test the efficacy of HA versus other established therapies of OA. Thus, both the Osteoarthritis Research Society International 2012 guideline and the American College of Rheumatology 2013 guidelines neither recommend nor discourage the use of HA [32]. Due to these reasons, this study is designed with an intent-to-treat, and therefore, the participants receiving HA or saline will be offered the opportunity to cross over to the Wharton’s jelly group after 3 months. Furthermore, the anecdotal evidence and unpublished case report from our team demonstrated that one injection is sufficient. The aforementioned study by Farr et al. also utilized one injection [5]. Therefore, in this study, we also proposed to utilize one injection only.

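### MOCART has no crossover-free randomised comparison of Wharton's jelly with control, because the only post-baseline MRI comes after controls may have switched

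*Protocol article*

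**What the plan says.** All of this is in the Protocol article.

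- **Endpoint** (Assessment points): one of the two listed secondary endpoints is to "assess the cartilage formation via MOCART at 1 year time point and compare it from baseline and between the groups".
- **Baseline scan** (Assessment points): visit 1 includes "a T2-weighted MRI to obtain a Magnetic Resonance Observation of Cartilage Repair Tissue (MOCART) score".
- **Imaging up to 3 months** (Assessment points): "Plain radiographs will be taken on visits 6 and 7". No MRI is listed for those visits.
- **Post-baseline scan** (Assessment points): at the end of follow-up, "plain radiographs will be taken again followed by an MRI on visit 9 for a MOCART score". Visit 9 is the 1-year visit.
- **Crossover** (Study interventions): "After the 3-month follow-up visit, patients injected with HA or saline will be offered the opportunity to cross over to the WJ group". It is the patient's choice. Those who accept receive WJ, and "they will receive an injection of WJ and will follow the schedule of events for the WJ injection group". Assessment points gives visit 2.2, immediately after injection, as the place where they re-enter the schedule.
- **Analysis principle** (Discussion): "this study is designed with an intent-to-treat". The same sentence gives the crossover offer.

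The article states no expected crossover uptake, and no effect size, standard deviation or power for MOCART.

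**The concern.** NPRS and KOOS are recorded several times up to the 3-month visit, so each has randomised comparisons made before any control can receive WJ. MOCART has none: its first post-baseline value comes after the crossover offer. By then a control who switched has had WJ for as long as a WJ patient has, yet under intent-to-treat counts as HA or saline.

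Two errors of interpretation could follow. A null between-arm result could be read as showing no cartilage effect, when dilution would explain it. Or the comparison could be moved to the controls who declined WJ, a self-selected group. No later analysis plan can repair this, because it cannot supply a scan that the schedule does not contain. MOCART is the endpoint chosen to measure cartilage formation, which the article both hypothesises and anticipates.

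**Working it through.** **1. Timeline from the visit schedule.** Visit 9 is 12 months after the injection that starts a patient's schedule. A control who crosses does so at 3 months or later, so the scan falls at 3 + 12 = 15 months or more after the first injection.

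| Patient | Months from first injection to visit 9 MRI | Months since WJ at that MRI |
|---|---|---|
| Assigned WJ | 12 | 12 |
| Assigned HA or saline, does not cross | 12 | none received |
| Assigned HA or saline, crosses | about 15 or more | 12 |

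In no row is a post-baseline MRI taken before the crossover offer. The third row rests on reading the restart as replacing the original schedule. The article does not say that a crossed-over patient also keeps the original 12-month visit. If such a visit were kept, its scan would be at most about 9 months after WJ (12 − 3), so it would still follow WJ.

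**2. What the by-arm difference estimates.** Let c be the share of controls who cross over and δ the true 12-month difference between WJ and control. Assume that a random share crosses, that late WJ gives the full effect, and that the extra 3 months make no difference. The control mean then rises by cδ, so

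expected by-arm difference = δ − cδ = (1 − c)δ.

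This is zero only at c = 100%. Of 56 controls per arm, 42 are still unexposed at visit 9 if c = 25%, 28 at 50%, 14 at 75% and 0 at 100%.

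**3. A benchmark effect.** The plan's own figure, at least 40 per group raised to 56, is for KOOS change at 3 months. It cannot be reproduced because no standard deviation is given. Solving backwards with two-sided α = 0.05 and 90% power:

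- Normal approximation: d = (1.960 + 1.282) × √(2/40) = 0.725. This implies a KOOS standard deviation of 8/0.725 = 11.0 or 10/0.725 = 13.8.
- Two-sample t-test: d = 0.734, used below.

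This value is borrowed from the KOOS sizing only to set a scale. It is not a MOCART effect.

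**4. Power with the diluted effect (1 − c) × 0.734** (two-sample t-test, two-sided α = 0.05):

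| Crossover share c (assumed) | Diluted d | Power, 40 per arm | Power, 56 per arm |
|---|---|---|---|
| 0% | 0.734 | 90% | 97% |
| 25% | 0.550 | 68% | 82% |
| 50% | 0.367 | 37% | 49% |
| 75% | 0.183 | 13% | 16% |
| 100% | 0 | no difference to detect | no difference to detect |

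**The case against.** The strongest reply is that randomisation is not lost. Crossover is voluntary ("If they decide to cross over, they will receive an injection of WJ"), and the article declares intent-to-treat. Comparing arms as assigned at visit 9 is a valid randomised comparison of two strategies. That stands. A reader might infer from the schedule that MOCART has no randomised contrast at all, and the documents do not support this: the contrast exists, but it is not WJ against untreated control.

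A second tempting inference is that the comparison can say nothing in favour of WJ. That does not follow either. Under the dilution model the difference is pulled towards zero, so a positive result would still be evidence for WJ, with its size understated. The unequal scan timing qualifies this, since three more months of follow-up in some controls could shift the score in either direction.

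Third, the power figures do not describe MOCART. This stands: effect, uptake and full benefit from late WJ are all assumed, and random crossing fits poorly with a choice left to patients. The figures show only how fast dilution acts.

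Fourth, MOCART is secondary, the cartilage expectation is worded mainly as change from baseline, crossover is openly offered to aid recruitment and retention, and details of handling crossed-over patients commonly belong in an analysis plan that is not shown. This limits the weight of the point. It does not remove it, because the article itself fixes the scan times, the crossover and the between-group claim, and these do not fit together.

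**Conclusion.** The concern holds in this form: MOCART has no crossover-free randomised comparison of WJ with HA or saline. What remains is a randomised comparison of immediate WJ with HA or saline plus optional WJ from 3 months. It shrinks to (1 − c) of the true difference under the stated assumptions, and scans in the control arms are not at a common time since randomisation (12 against about 15 months or more).

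The absence of a pre-crossover scan follows directly from the schedule. The 15-month figure rests on the natural reading of the restart. The size of the loss is unknown because the article gives no uptake; across 25% to 75% crossover the illustration runs from a moderate to a near-complete loss of power.

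This should be corrected, but it does not undermine the trial as a whole. The primary endpoints are safety and patient satisfaction, and the sample size rests on 3-month KOOS change, before crossover.

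**What to change.** In Assessment points, restate the between-group part of the MOCART endpoint as: *assigned to immediate WJ versus assigned to HA or saline with optional WJ from 3 months, analysed by randomised arm*. Add that:

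- the crossover share and the time from randomisation to the scan will be reported for each arm;
- a null result cannot be read as no cartilage effect of WJ relative to HA or saline;
- a positive difference is a diluted estimate;
- comparisons with controls who never crossed are descriptive, because crossover is self-selected.

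The accounts of the crossover schedule in Study interventions and Assessment points must also be reconciled with the 1-year time point in the endpoint, so that it is clear from which injection the year is counted for a crossed-over patient.

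The cost is wording in the endpoint list and the analysis plan, with no added MRI or patients. The downside is that the sponsor gives up a clean between-arm cartilage claim, which the present schedule cannot deliver.

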### Sample size and statistical analysis

A sample size calculation based on the initial analysis of change from baseline to 3 months was computed to determine the number needed per group to detect significance at the *α* = 0.05 level. To detect differences of 8–10 units in the KOOS, considered as the minimum clinical important difference (MCID), assuming an *α* of 0.05, *β* of 90%, and a 2-tailed test, the estimated sample size was calculated to be at least 40 subjects in each group, increased to 56 subjects in each group to allow for loss to follow-up. An interim analysis at the initial 3-month follow-up will allow us to examine the effect size and increase enrollment if necessary. The data will also be analyzed based on the age group, gender, and grade of osteoarthritis.

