We formulated a novel UC-derived WJ product that has been shown to contain the essential components of regenerative medicine, namely GFs, CKs, HA, and EVs [24]. In addition, the Wharton’s jelly has been reported to contain high amounts of extracellular matrix components, including collagen, hyaluronic acid, and sulfated proteoglycans, required to improve the treatment effect [24]. That study was an essential preliminary step to better characterize the WJ formulation before performing clinical trials to determine its safety and efficacy including providing symptomatic relief to patients with grade II or III knee OA.

The goal of the proposed study is to evaluate the safety and efficacy of intra-articular injection of UC-derived WJ for the treatment of knee OA symptoms. We hypothesize that there will be no difference in the outcomes in patients receiving injection of UC-derived WJ, HA, or saline in terms of safety. We also hypothesize that patients receiving intra-articular injection of WJ will show an improvement in their overall satisfaction, Numeric Pain Rating Scale (NPRS), Knee Injury and Osteoarthritis Outcome Score (KOOS), and cartilage formation over a period of 1 year compared to the baseline visit. Our null hypothesis is that there is no difference in patients receiving either WJ, HA, or saline, and no difference between baseline and after treatment within each treatment group over a period of 1 year.

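### The sample-size statement gives beta as 90% where power of 90% must be meant, and one n of 40 per group cannot be the exact 90% answer for both 8 and 10 KOOS points

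*Protocol article*

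**What the plan says.** The protocol article, under Sample size and statistical analysis, gives the whole power basis in two sentences. The calculation is "based on the initial analysis of change from baseline to 3 months". The target is a range: "To detect differences of 8–10 units in the KOOS, considered as the minimum clinical important difference (MCID"). The error rates are given as "assuming an *α* of 0.05, *β* of 90%, and a 2-tailed test". The result is that "the estimated sample size was calculated to be at least 40 subjects in each group, increased to 56 subjects in each group", the increase being an allowance for losses. No SD, loss rate, test or contrast is named. The same section plans an interim look at 3 months, at which the effect size is examined and enrolment may be raised.

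Elsewhere, the Participants section gives 168 in total, 56 per arm. The Randomization section gives 1:1:1 allocation to three arms. The Assessment points section lists KOOS among the secondary endpoints; safety and patient satisfaction are primary.

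**The concern.** Two things in the statement are wrong or cannot both be exact.

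First, beta is the probability of missing a true difference. A beta of 90% is a power of 10%, which nobody would plan for.

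Secondly, for fixed alpha, power and SD, the required n goes with the inverse square of the difference. A range of 8 to 10 points therefore gives a range of sample sizes, not one number. The article does not say which end produced 40. If it was the upper end, the trial has less than the intended power at 8 points, a value that the article itself counts as clinically important.

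This calculation is the only justification in the article for 168 participants. The interim look also needs a clear target difference and power against which to decide on enrolment, and the text supplies a range and a mislabelled error rate.

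**Working it through.** **Inputs from the article:** two-sided alpha 0.05; difference 8 to 10 KOOS points; 40 per group before and 56 after the allowance for loss (implied loss 1 − 40/56 = 28.6%). **Assumed:** 90% power is meant; the test is a two-group t-test on change in KOOS. **Not given:** the SD.

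**1. Can 40 be reproduced?** Not from the stated inputs, because the SD is missing. One can only solve for the SD that 40 implies.

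**2. The literal reading.** With 10% power, 40 per group and a 10-point difference, the implied SD is about 66 points (normal approximation). That is not a credible planning value, so beta of 90% is a mislabel of 90% power.

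**3. SD implied by 40 at 90% power.** The normal approximation gives a standardised difference d = (1.960 + 1.282) × √(2/40) = 3.242 × 0.2236 = 0.725. The exact noncentral-t solution (78 degrees of freedom) is d = 0.734. Then:
- solved at 8 points: SD = 8/0.734 = 10.9 (11.0 by the approximation);
- solved at 10 points: SD = 10/0.734 = 13.6 (13.8 by the approximation).

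**4. Ratio across the range.** (10/8)² = 1.56. One n cannot give exactly 90% at both ends.

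**5. Power under each origin of 40** (noncentral t):

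| 40 solved at | SD | Difference | Power, 40 per group | Power, 56 per group |
|---|---|---|---|---|
| 8 points | 10.9 | 8 | 90% | 97% |
| 8 points | 10.9 | 10 | 98% | over 99% |
| 10 points | 13.6 | 8 | 74% | 87% |
| 10 points | 13.6 | 10 | 90% | 97% |

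In the third row, 62 completers per group would be needed for 90% at 8 points (63 by the normal approximation).

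**6. Dependence on the SD.** Required n per group for 90% power, from n = 2 × (3.242 × SD/difference)², rounded up:

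| Assumed SD | n at 8 points | n at 10 points |
|---|---|---|
| 10 | 33 | 22 |
| 11 | 40 | 26 |
| 12 | 48 | 31 |
| 14 | 65 | 42 |
| 15 | 74 | 48 |
| 20 | 132 | 85 |

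The grid runs on both sides of the two implied values. Forty is enough over the whole range up to an SD of about 11, enough only towards the upper end between about 11 and 13.6, and too few throughout above that.

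**7. Change score against ANCOVA.** With equal SDs at baseline and 3 months and correlation ρ, the variance ratio of ANCOVA to raw change is (1 − ρ²)/(2(1 − ρ)) = (1 + ρ)/2. At an assumed ρ of 0.5 this is 0.75, or 25% less variance. At ρ of 0.3 and 0.7 it is 0.65 and 0.85.

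**The case against.** The best defence is that 40 may have been solved at the lower end. The article says at least 40. With an SD of about 10.9 or less, 40 per group gives at least 90% power everywhere from 8 to 10 points. On that reading the range is loosely worded but the sample size is sound. This stands, and nothing in the article rules it out. A reader might infer that the intended 90% is not delivered; without an SD, that cannot be shown.

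A journal article may also leave the SD and the loss rate to the full protocol or SAP, so their absence alone is no fault. That stands too. The SD is asked for here only because it is needed to interpret a figure that the article ties to two different targets.

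A reader might go further and infer that a three-arm trial was sized as a single two-group test, so that alpha is inflated or power lost to multiplicity. The null hypothesis, "Our null hypothesis is that there is no difference in patients receiving either WJ, HA, or saline", and the phrase "and a 2-tailed test" invite this. But no test or contrast is named. A three-group ANOVA with 40 per arm also gives 90% power if WJ differs from two equal arms, with an SD of 11.5 at 8 points or 14.3 at 10. Any multiplicity rule may sit in the SAP, which is not shown. The documents do not support that reading.

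Finally, KOOS is a secondary endpoint and the interim look allows enrolment to rise. Both limit the consequences. Neither corrects the mislabelled beta or says which difference 40 refers to.

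**Conclusion.** The point holds as an error of statement, not as a demonstrated failure of power. Beta of 90% is wrong as written and should be 10%. A single n of 40 cannot be the exact 90% answer at both ends of a range over which the required n changes by a factor of 1.56.

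The possible size is bounded by the two origins of 40. If it was solved at 8 points, there is no shortfall anywhere in the range. If it was solved at 10, power at 8 points is about 74% with 40 completers and 87% with 56. These figures assume that 90% power was meant, a two-group t-test at two-sided 0.05, and an SD equal to the one that 40 implies. A larger true SD would lower them and a smaller one would raise them; the article does not let the reader decide. No conclusion about multiplicity follows from the text.

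**What to change.** In Sample size and statistical analysis:

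1. Replace the beta figure by power of 90% (beta of 10%).
2. Name the one KOOS difference from which 40 was obtained, and the SD used.
3. If 40 was solved at 10 points, state the power that it gives at 8 points as well.

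This is a change of wording with no added patients. The only cost is that the stated power may look less favourable at 8 points.

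Separately, as an improvement rather than a correction: analyse 3-month KOOS by ANCOVA adjusted for baseline KOOS instead of raw change from baseline. Baseline KOOS is already collected, so this needs no new data or patients, only a line in the analysis section or SAP. The 25% reduction in variance depends on the assumed correlation of 0.5 and should not be counted in the stated power unless that correlation is supported.

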### Randomization

Participants will be assigned to a treatment group using sealed opaque envelopes coded with an alphanumeric identifier to ensure consecutive allocation of envelopes. Block randomization across all sites will be used to ensure even distribution to each group of 1:1:1 allocation to the 3 study arms—WJ, HA, and saline.

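### Enrolment may rise according to the observed 3-month effect size, and nothing beyond a two-tailed 0.05 is stated, so control of type I error is not assured

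*Protocol article*

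**What the plan says.** All of this stands in one paragraph of the Protocol article, under Sample size and statistical analysis.

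- The trial was sized by "A sample size calculation based on the initial analysis of change from baseline to 3 months", on the KOOS, "assuming an *α* of 0.05, *β* of 90%, and a 2-tailed test" (the 90% is read here as power). The result is that "the estimated sample size was calculated to be at least 40 subjects in each group", then "increased to 56 subjects in each group to allow for loss to follow-up".
- On the interim look: "An interim analysis at the initial 3-month follow-up will allow us to examine the effect size and increase enrollment if necessary".

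The paragraph does not name the endpoint whose effect size is examined. KOOS is the only outcome used for sizing and the look falls at the time point used for sizing, so 3-month KOOS change is the natural inference. Under Assessment points, KOOS is a secondary endpoint; safety and patient satisfaction are primary.

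**The concern.** Re-estimating a sample size from a nuisance parameter, such as the SD with the arms kept together, barely touches the error rate. Re-estimating it from the observed difference between arms is another matter. The final sample size then depends on the same data that enter the final test, and an ordinary pooled test at 0.05 no longer has a guaranteed 5% error.

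The wording commits to the second kind. An effect size between arms cannot be examined in the usual way without separating the arms, and the condition for adding patients is left open.

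The 3-month contrast also matters more than its secondary rank suggests. Under Study interventions, HA and saline patients may cross over to Wharton's jelly after the 3-month visit, so this is the last between-arm comparison before crossover is offered.

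**Working it through.** **Inputs from the article.** Two-sided α = 0.05; power 90%; difference 8–10 KOOS units; 40 per arm before and 56 after allowance for loss; 1:1:1 allocation; an enrolment increase driven by effect size at the 3-month look.

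**Assumptions, because the article gives no figure.** Information fraction at the look 0.25–0.9; cap on enrolment 1.5–3 times planned; several rules for the increase; a final pooled z-test at |z| > 1.96. Everything below concerns one two-arm contrast.

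**Step 1: the plan's own figure.** n per arm = 2(1.960 + 1.282)² SD²/δ² = 21.01 × SD²/δ². No SD is stated, so 40 cannot be reproduced directly. Solved backwards, SD = δ × √(40/21.01) = 1.380 × δ, which is about 11.0 for δ = 8 and 13.8 for δ = 10. The step from 40 to 56 corresponds to a loss of 1 − 40/56 = 28.6%.

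**Step 2: why the direction depends on the rule.** With n₁ per arm at the look (statistic z₁) and n₂ added afterwards, the pooled statistic is

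Z = (√n₁ z₁ + √n₂ x)/√(n₁ + n₂), with x standard normal under no effect.

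Given z₁, the chance of crossing the upper limit is P[x > (1.96√N − z₁√n₁)/√n₂], where N = n₁ + n₂; the lower limit is treated in the same way. Take a look at n₁ = 20, half of 40, and compare keeping N = 40 with raising it to 80.

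| z₁ | N | Upper cut-off for x | Lower cut-off for x | Chance of a false positive |
|---|---|---|---|---|
| 0.5 | 40 | 2.27 | −3.27 | 0.012 |
| 0.5 | 80 | 1.97 | −2.55 | 0.030 |
| 1.5 | 40 | 1.27 | −4.27 | 0.102 |
| 1.5 | 80 | 1.40 | −3.13 | 0.082 |

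Adding patients after a weak result raises the error; adding them after a fairly strong one lowers it.

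**Step 3: overall type I error.** These are simulations under no effect, planned n = 40 per arm, 1 million runs per setting (4 million for the rule with a success claim and for the combination test).

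| Rule at the look | Type I error |
|---|---|
| Reset n to 90% power at the observed effect, increases only, up to the cap | 0.052–0.061 |
| Go to the cap whenever conditional power is below 90% | 0.054–0.066 |
| Worst-case choice of n at each interim result | 0.054–0.081 |
| Increase only when conditional power is 50–90% | 0.039–0.049 |
| First rule, but no increase if the needed n exceeds the cap | 0.031–0.050 |
| Look with all planned patients, success allowed at 0.05, otherwise add 50%, 100% or 200% and re-test at 0.05 | 0.077, 0.083, 0.088 |

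**Step 4: with a protective test.** If the weights of the two stages are fixed from the planned stage sizes, Z = √t z₁ + √(1 − t) x, where t is the planned information fraction and x is the statistic from second-stage patients only. This is standard normal under no effect whatever n₂ was chosen. The simulated type I error is 0.04998.

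**The case against.** The strongest objection is that the article never says that the final test will be unadjusted. It gives 0.05 for the sizing calculation and does not describe the final critical value. A journal article commonly leaves decision rules, caps and alpha adjustment to the full protocol and SAP, which are not shown. This stands. A reader might infer that the final test stays at a naive 0.05, but the text does not establish it, and the absence of an adjustment is not itself the point here.

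Four other stronger readings are tempting and also lack support.

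- **A second chance at significance.** The 7.7–8.8% figures assume that success may be claimed at the look. The article's only stated action is to enlarge the trial.
- **Certain inflation.** Two plausible effect-based rules gave 5.0% or less.
- **Damage to the primary analysis.** The sizing variable is secondary, and the endpoint examined at the look is not named.
- **The trial team sees results by arm.** The article does not say who does the look. Under Discussion it already acknowledges unblinded investigators and notes that most endpoints are patient-reported.

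What the objection does not remove is the trigger. The article positively states that the observed effect size drives enrolment. An SAP could repair the test, but it cannot make that trigger a blinded one.

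**Conclusion.** The point holds in a limited form: a stated, effect-driven enrolment increase accompanied only by a two-tailed 0.05 does not assure type I error control.

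The size is modest on the natural reading, about 5.2–6.6% in place of 5%, with about 8% as the worst case. These figures rest on three conditions: an ordinary pooled final test at 0.05, patients added because the effect looks too small, and the assumed timing and caps listed above. They apply to the endpoint examined, by inference 3-month KOOS change, and to one two-arm contrast. The article confirms neither the first condition nor the exact rule, so the claim is that the error is unprotected as written, and not that it is known to be inflated.

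**What to change.** **Preferred.** In Sample size and statistical analysis, replace the observed effect size as the trigger with the blinded pooled SD of 3-month KOOS change, with the arms not separated. Hold the planned target difference fixed, as a single value within the stated 8–10 units, and cap the sample size. This leaves α essentially at 0.05. It also addresses the quantity on which the 40 per arm depends: the implied SD is 11.0–13.8, whereas an assumed SD of 15 would need 74 per arm for 8 units (21.01 × 225/64 = 73.9) or 48 for 10 units (21.01 × 225/100 = 47.3).

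**If an effect-based increase is kept.** Fix the rule and the cap before the look, have a statistician outside the trial team run it, and test with a pre-weighted inverse-normal combination of the two stages. State that the look permits no success claim. If one is wanted, two equally spaced looks need about 0.0294 at each in place of 0.05.

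**Cost.** Protocol and SAP wording, settled before the interim data are seen; the change itself adds no patients. The small downside of the blinded route is that enrolment can no longer react to an effect smaller than planned.
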